### Interventions

#### Neurodynamic exercises

The ‘active’ intervention is a progressive neurodynamic mobilisation adapted from our previously established protocol [35, 36]. Patients will attend a single session (~ 30 min) with an investigator who will instruct them the home exercise programme consisting of eight nerve and tendon gliding exercises (Fig. 2). The investigator will train patients with the help of a set of videos demonstrating the exercises on either the right or the left hand, as suggested by our patient partners. Patients will be asked to perform 10 repetitions of each exercise six times a day for six weeks (~ 1.5 min per session) in a manner that does not increase symptoms. These exercises are progressed on week 3 and 5th to increase the nerve gliding or tension as per each patient’s tolerance (Fig. 2, B and C, exercises in brackets). Patients will receive a leaflet detailing the neurodynamic exercises during their second baseline appointment (Suppl. Information. Appendix A), an exercise diary as well as a link to the exercise videos in weeks 1, 3 and 5. They will also be instructed to keep performing their usual activities but not start any new treatments during the 6 weeks of the study intervention (Suppl. Information. Appendix A).

**Fig. 2 Fig2:**
[figure not shown]
Progressive home-based programme of nerve and tendon gliding exercises (**A**) Weeks 1–2, (**B**) weeks 3–4, and (**C**) weeks 5–6. The brackets surrounding two figures indicate the combination of movements for that exercise, from the start to the end point

#### Steroid injections

Steroid injections are routine first-line treatment for patients with CTS [37] and will be used as a positive control group as they have established short term benefits [38, 39] and change nerve structure [40]. Patients in this group will receive a single injection of 40 mg depomedrone suspended in polyethylene glycol into the carpal tunnel (extraneurally) using the landmark technique [41]. Briefly, the needle will be inserted into the proximal carpal tunnel at the distal wrist crease immediately ulnar to the palmaris longus tendon [41]. A trained medical doctor will perform this technique as per standard practice at OUH NHS Trust. Participants will receive an information leaflet, and will be instructed to keep performing their usual activities but not start any new treatments during the 6 weeks of the study intervention (Suppl. Information Appendix B).

#### Advice group

The advice group will serve as a negative control group and will receive no additional intervention during the 6-week intervention period. Patients randomly assigned to this group will meet the investigator, who will provide them with an information leaflet detailing the advice (Suppl. Information Appendix C). Patients will be instructed to keep performing their usual activities but not start any new treatments during the 6 weeks of the study intervention.

Patients allocated to the advice group will be offered the 6-week home based exercise program as post-trial care (end of the 6-week treatment period) if they wish.

### Primary mechanistic outcome measure

#### Magnetic resonance neurography (MRN): Fractional Anisotropy (FA)

All participants will attend a MRN session on a 3 Tesla MAGNETOM Prisma scanner (Siemens, Germany) to visualise the median nerve at the wrist using a dedicated 16-channel wrist coil (Siemens, Germany).

Participants will be positioned in a ‘superman’ position, lying prone with the wrist above their head resting in the centre of the bore. The protocol includes the acquisition of multishell (b = 0, b = 300 and 800 s/mm^2^) diffusion-weighted imaging scans. In addition, true fast imaging with steady-state free precession (TRUFI) with/without magnetisation transfer (MT) preparation, and T2-mapping scanning will be acquired (see other markers in MRN). Scan parameters are summarised in Table 1.

**Table 1 Tab1:** MRI sequence parameters at the wrist

	3D TRUFI	T2 mapping	Diffusion Weighted Imaging (DWI)
Repetition time (TR)	10.1 ms	7,110 ms	4,000 ms
Echo time (TE)	4.14 ms	14.7–147 ms	47 ms
Flip angle (FA)	20°	Variable	90° and 180°
Field of view (FoV)	74.3 mm	225 mm	160 mm
Dimensionality	3D	2D	2D
Slice thickness	0.6 mm	1 mm	1 mm
Number of slices	176	50	50
In-plane resolution	0.1 × 0.1 mm	0.5 × 0.5 mm	1 × 1 mm
Echo spacing	N/A	N/A	0.96ms
Fat suppression	No fat saturation	Fat saturation	Fat saturation
Parallel acquisition technique	GRAPPA factor 2	GRAPPA factor 2	GRAPPA factor 2
Bandwidth	350 Hz/Px	132 Hz/Px	1220 Hz/Px
b values	N/A	N/A	0 (NSA = 8), 300 (NSA = 5), 800 (NSA = 8)
No. signal averages	1	1	8 (b = 0), 5 (b = 300), 8(b = 800)
Scan time single phase-encode blip (right-left or left-right)	N/A	N/A	6.42, 7.42
Total scan time (min)	10.16	10.32	14.18

N/A: not applicable; NSA: number of signal averages

All diffusion image pre-processing will be performed using the FMRIB Software Library (FSL) Diffusion Toolbox v 6.0 (Oxford, UK). Briefly, TOPUP [42, 43] and EDDY [44] tools will be applied to correct for distortions and eddy currents followed by DTIFIT [45] to compute the diffusion tensor model. FLIRT will be used to co-register the diffusion metrics to the anatomical sequences.

Median nerve region of interests will be determined at three levels: the distal radio-ulnar joint (proximal), pisiform (mid-carpal tunnel) and hook of hamate (distal carpal tunnel). Fractional anisotropy (no units) will be computed as our primary outcome measure.

### Secondary mechanistic outcome measures

#### Other markers in MRN of the median nerve at the wrist

The MRN protocol of the wrist includes the acquisition of true fast imaging with steady-state free precession (TRUFI) with/without MT preparation and a multi-spin-echo scan for T2-mapping scanning (Table 1). Multi-spin-echo and TRUFI will be processed using a custom-made Python script. TRUFI volumes acquired with different phases will be combined by calculating the square root of the sum of the squares of each volume. T2 maps will be obtained from the multi-spin-echo volumes using non-linear least-squares regression. FLIRT will be used to co-register the T2 maps to the high resolution anatomical images.

MR outcome measures of the median nerve will be computed at the three levels of the carpal tunnel described for the primary outcome measure (i.e., proximal, mid, and distal carpal tunnel). In structural images, we will compute the cross-sectional area (mm^2^) and flattening ratio (arbitrary units). Mean diffusivity (mm^2^/s), and radial/axial diffusivity (mm^2^/s) will be obtained from diffusion images. Finally, T2 (ms), and magnetisation transfer ratio (arbitrary units) will be computed from their respective sequences. Metrics derived from multishell data will be explored.

#### Somatosensory function

We will use the standardised Quantitative Sensory Testing (QST) battery of the German Network for Neuropathic pain [46] to evaluate the somatosensory function over the median nerve territory of the studied hand.

Thermal thresholds will be explored with series of three repetitions to compute the average temperature (°C) for cold and warm detection thresholds (CDT, WST), hot and cold pain threshold (HPT, CPT) and five repetitions for thermal sensory limen (TSL) using a Thermotester (Somedic, Sweden, 25 × 50 mm thermode). Paradoxical heat sensations (PHS) will be recorded during TSL testing. Pain ratings during HPT and CPT will be recorded on an 11-point numerical rating scale (NRS), from ‘0’ representing no pain to ‘10’, worst pain imaginable and averages used for analyses.

Mechanical detection thresholds (MDT) will be assessed using five series of ascending/descending von Frey monofilaments (mN, geometric mean calculated). Mechanical pain threshold (MPT) will be explored with a set of weighted pinpricks (mN, geometric mean calculated). Mechanical pain sensitivity will be examined with a NRS of 0–100 using a shortened protocol of two sets of seven pseudo-random pinprick stimulations [47]. Dynamic mechanical allodynia (DMA) will be explored [26, 48] using a cotton wisp, cotton wool tip, and a standardised brush (Somedic, Sweden) [46] that will be interleaved during the MPS assessment. The geometric mean will be calculated for MPS and DMA. Wind-up ratio will be calculated as the average pain rating on a 100-NRS scale between three trains of 10 pinprick stimuli divided by three single stimuli. Vibration detection threshold (VDT) will be determined as a disappearance threshold through the average of three repetitions using a Rydel Seiffer tuning fork (64 Hz, 8/8 scale). Pressure pain threshold will be determined as the average of three series of ascending stimulus intensities (kPa) using a manual algometer (Wagner Instruments, USA).

All stimuli will be first demonstrated over the lateral, proximal forearm (radial territory) of the non-studied side, with the exception of VDT which be shown over the ulnar styloid. All thermal and mechanical stimuli will then be assessed over the palmar aspect of the index finger (proximal phalanx), except VDT (over the second metacarpophalangeal head) and PPT (over the thenar eminence). Additionally, pain thresholds including HPT, CPT, MPT and PPT will be assessed in the contralateral lower limb (upper anterolateral aspect of the tibialis anterior muscle) to determine potential effects on generalised hypersensitivity.

QST outcome measures will be transformed into Z-scores [46] using our healthy control participants as well as existing control data sets [26, 49], who will be matched for age and sex. Additionally, we will classify each participant with CTS to a specific and unique somatosensory profile [50]: (1) sensory loss; (2) thermal hyperalgesia; or (3) mechanical hyperalgesia.

#### Neurophysiological function

We will use surface electrodes to measure the median SNAP amplitudes (µV), CMAP amplitudes (mV) and conduction velocities (m/s), as described above [32].

#### Neurodynamic tests

We will explore the mechanosensitivity of the median, ulnar and radial nerve using Upper Limb Neurodynamic Tests (ULNT) in patients bilaterally [12]. The median nerve bias test (ULNT 1) will be performed with the patient lying supine and the movement sequence will involve maximum end range shoulder abduction, wrist and finger extension, forearm supination, shoulder external rotation and elbow extension [12]. The ulnar nerve bias (ULNT 3) sequence starts with the patient lying supine and their arm resting by the side followed by wrist extension, forearm pronation, elbow flexion, shoulder external rotation, shoulder girdle depression and shoulder abduction [12]. The radial nerve bias (ULNT 2B) starts with the patient in supine and diagonally on the plinth. The sequence involves shoulder girdle depression, elbow extension, forearm pronation, wrist and finger flexion, followed by shoulder abduction [12]. The end point of these tests is the first onset of symptoms (P1). The test will be considered positive if (1) patient’s symptoms are at least partially reproduced, and (2) structural differentiation (away from the site of pain) changes the symptoms [51].

We will also quantify the elbow extension angle at P1 with an inclinometer in a slightly modified ULNT1 manoeuvre. The testing will involve shoulder at 90 degrees abduction, neutral shoulder rotation, wrist and fingers extension and finally, elbow extension. This assessment will be performed in patients and healthy participants (reference values).

#### Pinch grip strength

Tip to tip pinch of the thumb and index finger, key pinch between the radial side of index finger and thumb, and tripod pinch using the thumb, index and middle finger (kg, averaged 3 repetitions) will be assessed using a mechanical pinch gauge dynamometer bilaterally (B&L Engineering, CA, USA) as per standard recommendations [52, 53].

#### Self-reported outcome measures

We will use a battery of validated questionnaires to evaluate patients’ symptoms, functional deficits, quality of life, sleep, and psychological co-morbidities at all time points. Patients assigned to the neurodynamic exercise group will be asked to complete an exercise diary daily (electronically or on paper) to monitor adherence for the duration of the intervention (6-weeks). Healthy participants will only complete questionnaires determining function, quality of life, sleep and psychological comorbidities (Table 2).

**Table 2 Tab2:** List of questionnaires

Questionnaire	Type of outcome measure	Baseline	6 weeks	6 months
*Assessment of pain intensity and location*: • Boston Carpal Tunnel questionnaire [59] • Paper based or electronic body diagram to localise symptoms • Subject reported average intensity of pain, paraesthesia and numbness. Reported on 10 cm visual analogue scales ranging from no symptoms to worst symptoms ever. • Central sensitisation index (CSI) [60]	Secondary Descriptive Descriptive Secondary	x	x	x
*Assessment of functional deficits*: • Quick DASH [61] (healthy) • Patient specific functional scale [62, 63]	Secondary	x	x	X
*Neuropathy Screening tools*: • DN4 [64] • painDETECT [65]	Secondary	x	x	x
*Assessment of neuropathic pain symptoms*: • Neuropathic Pain Symptom Inventory [64]	Secondary	x	x	x
*Assessment of psychological co-morbidity*: • Depression Anxiety Positive Outlook Scale (DAPOS) [66] (healthy) • Pain Catastrophising Scale (PCS) [67] (healthy) • Short-form Pain Anxiety Symptoms Scale (PASS-20) [68] (healthy)[62]	Secondary	x	x	x
*Assessment of sleep interference*: • Insomnia Severity Index [69] (healthy)[62]	Secondary	x	x	x
*Assessment of quality of life*: • EQ-5D-5 L [70] (healthy)	Secondary	x	x	x
*Assessment of longitudinal change*: • Global rating of change questionnaire [71]	Secondary		x	x
*Assessment of medication/diagnoses*: • Medications/diagnoses questions (see unvalidated questionnaires) (healthy)	Descriptive	x	x	x

All listed questionnaires are to be completed by patients. After the name of the questionnaire, we have indicated in brackets which ones will also completed by healthy control participants

### Exploratory outcomes

#### Blood inflammatory markers (e.g., cytokine panels)

We will collect 26 ml of venous blood from antecubital venepuncture. Serum will be extracted from whole blood collected into BD Vacutainer SST tubes (gold cap) and centrifuged at 1.3 g for 10 min at 4 °C 30 min after venepuncture. Serum fraction will be immediately frozen at -80 degrees and stored for batch processing in accordance with the Human Tissue Act. In future analyses, we can explore the concentrations of serum inflammatory protein levels and other markers of interest, including but not limited to TGF-β, CCL5, and IL-4, as per our previous work [28].

For future analyses and biobanking, we will also sample blood into RNA stabilising tubes (Tempus™ blood RNA tube, Fisher Scientific), serum clot activator tubes (red cap BD, Wokingham UK) and EDTA containing tubes (lavender cap, BD, Wokingham UK).

#### Cutaneous markers (e.g., inflammatory markers, innervation markers)

Future exploratory analysis will involve looking at the presence of inflammatory and innervation markers via 3 mm skin punch biopsies performed on the ventrolateral side of the proximal phalanx of the index finger [48] (baseline and 6 weeks in patients, baseline only in healthy controls). In patients, the 6-weeks biopsy will be performed slightly more proximal, avoiding the primary biopsy site as we have previously done [26]. Samples will be processed for immunostaining (fixation in fresh periodate-lysine-paraformaldehyde for 30 min before being washed in 0.1 M phosphate buffer and cryoprotected in 15% sucrose in 0.1 M phosphate buffer and freezing in optimal cutting temperature gel at -80 degrees) and molecular experiments (snap freezing in liquid nitrogen before storing at -80 degrees).

#### MRN markers at the DRG

As preclinical literature suggests changes at the level of the DRG after peripheral nerve injury [54, 55], all participants will be scanned to visualise their cervical DRG with a 64-channel head/neck coil (Siemens, Germany). Participants will be lying supine. The protocol includes T2 weighted (T2W) and Diffusion Weighted (DW) scans. T2W and DW images will be acquired using Sampling Perfection with Application optimised Contrast using different flip angle Evolution (SPACE) and Readout Segmentation Of Long Variable Echo trains (RESOLVE) sequences, respectively. DW images will be registered to T2W images (Supplementary Table 1).

MR outcome measures will be obtained from structural images, such as volume (mm^3^) for the DRG. FA, mean diffusivity (mm^2^/s), and radial/axial diffusivity (mm^2^/s) will be calculated from diffusion images. Metrics derived from multishell data will be explored.

### Additional cohort characterisation

#### Demographic variables

We will collect demographic data on age, sex, height, weight, ethnicity, profession, working status, and years of education. Medical information will include the most affected side, presence of unilateral/bilateral symptoms, duration of symptoms, previous history of carpal tunnel syndrome (personal and in the family), previous treatment received for carpal tunnel syndrome (CTS), current and previous medications, smoking and alcohol intake.

#### Clinical assessment

Patients will complete two body charts, one reflecting the presence of symptoms in their body, and a detailed diagram of hand symptoms. Patients will undergo a detailed neurological examination which will include upper limb myotome testing (C4-T1) recorded on the five-point British Medical Research Council scale (M0 = no contraction, M1 = flicker or trace of contraction; M2 = active movement, with gravity eliminated; M3 = active movement against gravity; M4 = active movement against gravity and resistance; M5 = normal power) [56]; biceps, triceps and brachioradialis reflexes recorded as normal, absent, reinforced or hyperreflexia (adapted from National Institute of Neurological Disorders and Stroke Scale (NINDS) [57], and exploring potential loss of sensation to light touch and pinprick recorded as absent, reduced, normal or increased on two separate body charts.

### Safety and adherence to neurodynamic exercises

Patients assigned to the neurodynamic exercise group will be asked to complete an electronic (or paper-based) exercise diary daily to monitor treatment adherence for the duration of the intervention (6-weeks). Patients will be asked to indicate how many times they perform the exercises each day.

We will also use periodic phone calls during the 6-week study period (3rd day after randomisation, weekly thereafter) to check on progress in each of the intervention groups, decrease study attrition, give advice on exercise performance when needed, check if there are potential adverse events associated with the exercise intervention or the steroid injection, and to confirm that they have not started any new treatments during the intervention period in the steroid and advice groups. This was suggested by our patients’ partners to increase adherence.

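### The calls check for new treatments in the steroid and advice arms only, although all three arms are under the same restriction, so co-treatment is followed less closely in the exercise arm

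*Protocol article*

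**What the plan says.** The restriction on other treatments is the same in each arm. The exercise section says: "They will also be instructed to keep performing their usual activities but not start any new treatments". The steroid section says that participants "will be instructed to keep performing their usual activities but not start any new treatments during the 6 weeks", and the advice section says "Patients will be instructed to keep performing their usual activities but not start any new treatments". In every case the restriction covers the 6-week intervention period.

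The section Safety and adherence to neurodynamic exercises describes telephone calls during that period ("3rd day after randomisation, weekly thereafter"). They are meant "to check on progress in each of the intervention groups", so every arm is called. The same sentence then gives two purposes that depend on the arm. The first is to "check if there are potential adverse events associated with the exercise intervention or the steroid injection". The second is "to confirm that they have not started any new treatments during the intervention period in the steroid and advice groups".

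Two other sources bear on the point. Table 2 lists medication and diagnosis questions for all patients at baseline, 6 weeks and 6 months, classed as descriptive. The exercise arm also keeps a daily diary, in which patients record how often they did the exercises.

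**The concern.** The instruction is common to all arms and the calls reach all arms, yet the stated check on that instruction leaves out the experimental arm. A question repeated at each call does two things: it records new treatments, and it reminds the patient not to start any. As written, both effects operate in the control arms and neither in the exercise arm.

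This matters more here than in many trials. The Background section explains that earlier human evidence came largely from exercises combined with other conservative care, and that what the exercises do on their own is still open. Co-treatment in the exercise arm is the confounder the design is meant to remove. If it is under-recorded there, a change caused by a splint, a drug or other therapy could be read as a mechanism of the exercises, and the by-arm description of co-treatment could not be taken at face value.

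**Working it through.** The plan gives no figure on this point, so there is none to reproduce. The check sets side by side what the article states for each arm.

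| Item (section of the protocol article) | Exercise | Steroid | Advice |
|---|---|---|---|
| Told not to start other treatments for 6 weeks (the three intervention sections) | yes | yes | yes |
| Called on day 3, then weekly (Safety and adherence) | yes | yes | yes |
| New-treatment check stated for the calls (Safety and adherence) | not stated | yes | yes |
| Adverse-event check stated for the calls (Safety and adherence) | yes | yes | not stated |
| Medication and diagnosis questions at 6 weeks (Table 2) | yes | yes | yes |
| Daily exercise diary (Safety and adherence) | yes | no | no |

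1. **New treatments.** The steroid and advice arms have two stated routes, the calls and the 6-week questions. The exercise arm has one, the 6-week questions.
2. **Does the common questionnaire close the gap?** In part. By its title it covers medication, so drugs started in any arm have a stated route of capture. The title does not mention splints, manual therapy or other non-drug care, and the content is not shown. Within the intervention period it is asked once, at the end, and it does not remind patients of the restriction along the way. Even if it captured everything, the arms would still differ in how often they are questioned.
3. **Does the diary close it?** No. It is described as a count of exercise sessions.
4. **Adverse events.** The stated check covers the exercise and steroid arms. Only the steroid arm has both call checks stated.
5. **Illustration of scale, on an assumed rate.** The document gives no rate of co-treatment. If 10% to 20% of an arm of 26 started something new, that would be 0.10 × 26 = 2.6 to 0.20 × 26 = 5.2, or about 3 to 5 patients. This is how many patients the weaker ascertainment would apply to. It is not a count of missed cases, because the 6-week questions would find some of them, and it says nothing about the effect on fractional anisotropy.

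**The case against.** **The sentence is a summary, and the call script may sit in the full protocol.** An article does commonly leave a call script to the full document, and this one does not say that the question is withheld from exercise patients. A flat claim that they are never asked would go too far. But the article is not silent here: it names the arms to which the check applies and leaves one out, having just said that every arm is called. That is a stated rule for particular arms. The authors may have had in mind control patients taking up exercises, but they do not say so, and the wording covers new treatments in general.

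**There is a common instrument.** This stands for medication. A reader might infer that anything started by exercise patients would go undetected. Table 2 does not support that: all patients answer the medication and diagnosis questions at 6 weeks, and exercise patients are also telephoned about progress and seen at follow-up.

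**The bias is not shown.** This also stands. The primary outcome is an imaging measure, and the outcome examiner and the statistician are blinded. Nothing in the document shows that a treatment started within 6 weeks would move fractional anisotropy, or which way. A reader might infer a bias in favour of exercise; the text supports only the possibility of wrong attribution.

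**Harms.** A reader might infer that harms in the exercise arm have no comparator. That is wrong, because the randomised steroid arm is checked too. The advice arm gets no active intervention, so a check limited to intervention-related events leaves it out almost by definition. No safety outcome is listed, and a general adverse-event procedure may exist in the full protocol. What is missing from the article is an untreated background rate, which is a minor matter.

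**Conclusion.** The point holds for co-treatment, and it is modest. Followed as written, the plan monitors and reinforces an identical restriction unequally: by calls and a 6-week questionnaire in the control arms, by the questionnaire alone in the exercise arm. Co-treatment in the exercise arm could be under-recorded, most plausibly for non-drug treatments, and its effect attributed to the exercises.

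The conclusion rests on two assumptions: that the calls follow the sentence as printed, and that the medication and diagnosis questions do not fully cover non-drug care. If exercise patients are in fact asked the same question, what remains is an error of wording. The size and direction of any bias in fractional anisotropy cannot be estimated, and the design is not invalidated. The adverse-event difference is a small addition and would not justify a change alone.

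**What to change.** - Amend the sentence under Safety and adherence to neurodynamic exercises so that the same new-treatment question, recording type and start date, is asked on every call in all three arms.
- Tabulate new treatments by arm beside the 6-week results.
- If calls have already been made, report what was asked in the exercise arm. If all arms were asked, correcting the sentence settles the matter. If not, say so when the by-arm figures are presented, since the missing answers can now be recovered only by recall.
- As a minor addition, put the adverse-event question to the advice arm too, so that events in the exercise and steroid arms can be read against an untreated background rate.

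The cost is the wording of the call script and one descriptive table. The calls already go to every arm, and neither the sample size nor the primary analysis changes.
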